### Sample size calculation

Sample size calculations were based on the expected effects of the intervention on the main outcome measure, the percentage of people sustaining a fall during one year of follow-up. The study by Close et al. [5] found that the percentage of persons who sustained a recurrent fall was 52% in the usual care group and 32% in the intervention group. If we want to detect the same reduction in the percentage of persons sustaining a recurrent fall in our study, with a power (1-beta) of 90% and alpha of 0.05, we need 123 patients in each group (a total of 246). Based on the experiences of Close et al. and our own experiences in trials among elderly people in the Netherlands [14], we expect a dropout rate of about 25% during the one-year follow-up period. This means that about 164 persons per group (a total of 328) have to be included in the study. The inclusion period was 14 months.

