### Economic evaluation

The economic evaluation in our study is being performed from a societal perspective, which implies that all costs and outcomes are taken into account if possible. The economic evaluation will be a combination of a cost-effectiveness and a cost-utility analysis. The primary outcome measure for the cost-effectiveness analysis will be the percentage of people sustaining a fall during one year of follow-up. As mentioned above, falls are recorded by means of a calendar. Within the cost-utility analysis, the effects are measured in terms of generic health-related quality of life descriptions, measured according to the standard Dutch version of the EuroQol (EQ 5-D) [20] in self-administered questionnaires at baseline and after four and twelve months. A direct value for every state of health is generated using the social tariff [24], which involves an algorithm for interpolating EuroQol results to population utilities.

We will assess programme costs, healthcare costs and patient and family costs. All costs are measured by means of a cost diary [25], in which patients continuously record volumes of health care utilisation during the twelve-month follow-up period. Subjects are asked to report their cost diary relating to the previous month during the same monthly telephone interview in which they report falls from the calendar. The volume of each category we measure will be multiplied by the cost price of each category. Cost prices are presented in Euros. Health care costs are estimated according to the Dutch guideline for cost analysis in health care research [26]. Where such guidelines are not available for a specific category, real costs or tariffs are used to estimate costs.

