### Analysis

Data will be primarily analysed according to the intention-to-treat principle, i.e., including all participants with valid data, regardless of whether they received or did not receive the intervention. Subsequently, the results of the intention-to-treat analysis will be compared with the results of an on-treatment analysis, to assess whether protocol deviations have caused bias. Participants with documented deviations from the study protocol (i.e., participants in the intervention group who did not receive the entire intervention or participants in either the intervention or the control group with incomplete follow-up data) will be excluded from this on-treatment analysis.

Comparability between the intervention and control groups will be assessed at baseline to check for differences between the two groups. Outcome at four and twelve months will be compared between the intervention and control groups by both univariate and multivariate techniques. We will use multivariate analysis to adjust for possible differences in baseline scores and background variables between the intervention and control groups. Dropouts and losses-to-follow up will be described.

The economic evaluation will involve calculating cost-effectiveness and cost-utility ratios. The additional costs and additional benefits of the intervention programme compared with usual care will be examined by calculating incremental cost-effectiveness and cost-utility ratios. These incremental ratios represent the difference in mean costs between the intervention and usual care groups in the numerator and the difference in mean effects in the denominator[27].

Since the recruitment period is only 14 months, and the follow-up period is also relatively short (12 months), it is unlikely that there will be substantial differences between costs made by and for patients who started in the first part of the recruitment period and those who started in the last part. Therefore, discounting of costs is not required. Finally, a sensitivity analysis will be done to assess the generalisability of the assumptions made in the costing process. This sensitivity analysis, which involves calculating the upper and lower limits of the confidence interval of cost and effect variables, will allow us to explore and quantify the uncertainty not related to sampling variations.

The process evaluation will mainly be analysed by means of descriptive techniques.

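### The sensitivity analysis offers confidence limits as the test of the costing assumptions, but such limits measure sampling variation only and vary no price

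*Protocol article*

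**What the plan says.** The Analysis section of the protocol article gives the purpose: "a sensitivity analysis will be done to assess the generalisability of the assumptions made in the costing process". It then describes the method as calculating upper and lower confidence limits and states what these deliver: the "limits of the confidence interval of cost and effect variables, will allow us to explore and quantify the uncertainty not related to sampling variations".

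The same section defines the incremental ratios as "the difference in mean costs between the intervention and usual care groups in the numerator and the difference in mean effects in the denominator".

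The Economic evaluation section shows what the costing assumptions are. Costs are built from volumes and prices: "The volume of each category we measure will be multiplied by the cost price of each category". Prices come from a Dutch guideline, with a fallback: "Where such guidelines are not available for a specific category, real costs or tariffs are used to estimate costs". Programme costs are one of the cost groups. For the effect side, "The primary outcome measure for the cost-effectiveness analysis will be the percentage of people sustaining a fall during one year of follow-up".

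**The concern.** Purpose, method and claimed result do not fit together. The purpose is to test choices made in costing. The method is a measure of sampling variation. The claimed result is a measure of everything except sampling variation.

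Cost-effectiveness from a societal perspective is one of the two research questions, and the Discussion ties implementation to effectiveness and cost-effectiveness both being shown. If the text is followed, a reader of the results would believe that the economic conclusion had been checked against other prices and tariffs, when every figure had been computed at a single set of them.

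**Working it through.** **1. The plan's own figures.** The economic text states no number, so the check starts from the sample size, which supplies the fall rates and group size used below. The inputs are "52% in the usual care group and 32% in the intervention group" and "with a power (1-beta) of 90% and alpha of 0.05, we need 123 patients in each group (a total of 246" (Sample size calculation).

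Unpooled normal formula, two-sided alpha 0.05, power 0.90:

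n = (0.52 × 0.48 + 0.32 × 0.68) × (1.960 + 1.282)² / 0.20² = 0.4672 × 10.51 / 0.04 = 122.7, rounded up to 123. With 25% dropout, 123 / 0.75 = 164.

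Both stated figures reproduce, and nothing in this point affects them.

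**2. What the effect limits measure.** For the planned difference of 0.20, the 95% limits are 0.20 ± 1.96 × √(0.4672 / n):

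| n per group | Lower | Upper | Width |
|---|---|---|---|
| 123 | 0.079 | 0.321 | 0.242 |
| 166 | 0.096 | 0.304 | 0.208 |
| 1,230 | 0.162 | 0.238 | 0.076 |
| 12,300 | 0.188 | 0.212 | 0.024 |

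The width goes to zero as n grows, which is the mark of sampling variation. No price enters the formula, so the limits of the fall outcome cannot bear on a costing assumption at all.

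**3. What the cost limits measure.** For one cost category with price p, mean volume v and volume standard deviation s, the limits of mean cost are p × (v ± 1.96 × s / √n). The price is a fixed multiplier. If it changes by a factor k, both limits change by k, whatever the distribution of volumes. The interval therefore carries no information on whether p is right.

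Illustration with assumed values, since the article gives none: Poisson volumes with mean 5 (so s = √5) and prices of 100 and 200.

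- n = 166: √(5 / 166) × 1.96 = 0.340. Limits are 466 to 534 at price 100, and 932 to 1,068 at price 200.
- n = 16,600: √(5 / 16,600) × 1.96 = 0.034. Limits are 496.6 to 503.4 at price 100, and 993.2 to 1,006.8 at price 200.

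Neither interval covers the other. With more patients, each closes in more tightly on the answer that its own price implies.

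**4. Separate limits and the ratio.** Write R = ΔC / ΔE for the incremental ratio. To first order,

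Var(R) ≈ [Var(ΔC) + R² Var(ΔE) − 2R Cov(ΔC, ΔE)] / ΔE².

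Separate limits for cost and for effect use the two variances and leave out the covariance. They describe each component but do not by themselves give an interval for the ratio.

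**The case against.** **It is a slip, and the word *not* should simply be struck out.** That would make the last clause true, but the sentence before it would still present confidence limits as the test of the costing assumptions.

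**Confidence limits are sometimes used as input ranges in a one-way sensitivity analysis.** They are, and this is legitimate. It still explores sampling error, and no price, tariff or programme cost moves.

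**The text says that the sensitivity analysis involves these limits, not that it consists only of them.** This is fair, and a fuller plan might also vary prices. It does not rescue the statement that confidence limits quantify non-sampling uncertainty.

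Two stronger readings are tempting, and the document supports neither.

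- A reader might infer that the incremental ratios will have no valid sampling interval. The article does not say that this is the only uncertainty analysis, and a condensed article may leave a bootstrap or other joint interval to a fuller plan that is not shown.
- A reader might infer that cost limits will be divided by effect limits to form a range for the ratio, and might try to say how far that range is too wide. The article describes no such division. Any figure would depend on an assumed cost difference, cost standard deviation and cost-effect correlation, none of which it gives.

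**Conclusion.** The point holds as an error in the stated method. The described analysis cannot test the costing assumptions, and its result would carry the wrong label. This conclusion rests on what a confidence interval is and on the article's own account of how costs are built. It does not depend on the assumed prices or volumes above, which only illustrate it.

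The scope is limited. The defect touches the uncertainty analysis of the economic evaluation only. Randomisation, the fall and daily-functioning outcomes, the sample size and the definition of the incremental ratios are unaffected. No excess width or bias in euros is claimed. On the ratios, the conclusion goes no further than this: as described, separate limits for cost and effect do not amount to an interval for the ratio.

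It should be fixed before the economic results are analysed, but it does not threaten the trial.

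**What to change.** Replace the sentence with two separately labelled analyses.

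1. **Costing assumptions.** Deterministic one-way or scenario analyses that vary unit prices, the choice between tariff and real cost where no guideline price exists, and programme cost per participant. State the range for each and its source in advance.
2. **Sampling uncertainty.** Label confidence limits for costs and effects as such. For the incremental cost-effectiveness and cost-utility ratios, use a joint method, for example a non-parametric bootstrap that resamples patients' cost-effect pairs within each group. A cost-effectiveness plane or acceptability curve is a useful way to show the result, but the correction does not depend on it.

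The cost is revised wording and a little more analysis. Volumes are recorded per patient and priced afterwards, so both re-pricing and resampling can be done on data already being collected.

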### Progress of the study

Recruitment of eligible subjects commenced in December 2002 and ended in February 2004, resulting in a total of 333 eligible subjects being included in the trial. Randomisation resulted in the allocation of 166 participants to the intervention group and 167 to the control group. Of the 333 persons recruited, 105 (32 %) are male and 228 (68 %) are female.

The follow-up period is to end in May 2005. Results on the effects of the programme will be available in 2006 and will be published in the relevant journals.

## Discussion

Although the intervention has been subject of earlier research, this study will provide new information about the effectiveness in the Dutch situation. Furthermore, the results of the economic evaluation can provide information about the cost-effectiveness of the intervention and the effects on quality of life. In case of shown effectiveness and cost-effectiveness, we aim to implement this intervention into usual healthcare.
